### Representativeness of the sample and sample selection (at cluster level)

To control for internal representativeness homogeneity tests are applied in order to verify that the two treatment groups are homogenous and in order to test for potential bias due to drop-outs or missing values. To prove that our sample is similar to the German population of immigrants that take part in integration courses nationwide (control of external representativeness) the BAMF questionnaire is applied.

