### Sample size calculation - power analysis

The sample size calculation resp. power analysis is based on *α* = 0.05 at a power of 0.80, using pilot data concerning the number of participants in the language courses. Concerning the different primary outcomes (children’s stress level, language development, socio-emotional development and mothers’ integration) we expect effect sizes of at least *d* = 0.5. Then the sample size for analysis of variance in a RCT study would be *n* = 63. But we applied a CRCT study. Therefore we have to correct the *n* in a corrected *n** according to the following formula introduced by Eldridge et al. (2006), providing a conservative estimate of sample size requirements for trials using cluster-level analyses weighted by cluster size:$$ n* = \left\{\ 1 + \left[\ \left(1+CV{}^2\right)\ \mathrm{x}\ \mathrm{m}\ \hbox{--}\ 1\ \right]\ \mathrm{x}ICC\right\}\ \mathrm{x}\ n $$

The formula consists of the coefficient of variation *CV* for trials with unequal cluster sizes (that means with unequal sizes of language courses) and the intraclass-correlation coefficient *ICC* within the clusters and the mean cluster size *m*. Using the findings of a pilot study, the estimated coefficient of variation is *CV* = 0.4 (rather smaller) and the estimated intra class correlation coefficient (based on the pre-post differences including the *CV*) *ICC* = 0.1 (rather smaller). Furthermore, we expect a mean cluster size of *m* = 2 pregnant women in each course (cluster).

The corrected sample size would therefore be *n** = 1.132 × 63 = 71.32. Thus the minimum sample size would be 72 pregnant women per treatment and resp. 36 integration courses should be selected per treatment. However under consideration of a 20 % drop-out rate the corrected minimum sample size is *n** = *n** × 1.25 = 90 women per treatment and thus a number of 45 courses per treatment should be selected (see Fig. 2).

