### Statistical analysis

The design is an analysis of variance design with repeated measures. The main instruments for analysis applied are Analysis of variance (ANOVA) as well as Analysis of covariance (ANCOVA) models. The main factor is the intervention group (A or B) and the most relevant secondary factor is the initial value (baseline value). All baseline characteristics will be described at the individual level. Relevant characteristics will be added if applicable as covariates to the models. Six main assessments encompass the treatment phase and follow-up.

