## Discussion

This trial has one major goal: to compare the effectiveness of two different interventions on the development of children with an immigrant background in Germany and the integration of their mothers. Based on empirical findings it is expected that professionally supported good early relationship experience improves long-term integration of immigrant children. In a prospective randomized comparison group design the project aims at evaluating the implementation as well as the short- and long-term effectiveness of FIRST STEPS (intervention A) in comparison to an intervention being offered by paraprofessionals (intervention B). Anticipated is that supporting the earliest parent-child-interactions and parenting capacities in a professional psychoanalytically oriented intervention (A) will have a greater positive impact on the mothers’ integration, on children’s affective, socio-emotional and cognitive development and on the quality of the parent-child relationship than the intervention provided by paraprofessionals with an immigrant background in the more open “mother-child groups” (B). We tried to reach comparable doses of intervention in the course of the 3 years of intervention for ensuring that effects would be caused by the type of intervention and would not just be a matter of more or less intervention.

In any case, number and timing of group sessions and individual contacts will be documented. In this trial, a high quality is assured by an independent assessment. Due to the high expected attrition rate in this population at risk, drop-out is thoroughly documented and respective analyses are being planned.

As mentioned before, high quality evaluation of prevention projects for young children with an immigrant background and their families have been scarce and to our knowledge an RCT comparison group design is non-existent in Germany. Thus the study has the status of a model project. If the prevention offers prove to be effective and sustaining, the empirically based prevention programs may be implemented in other German cities and migrant populations as well. Thus the study will prove to have a practical and political relevance.

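### Homogeneity tests at this sample size cannot show that the arms are alike or that drop-out causes no bias, and three of the four primary outcomes have no baseline value to adjust for

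*Protocol article*

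**What the plan says.** Three places in the protocol article bear on this point.

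- **Representativeness of the sample and sample selection:** "homogeneity tests are applied in order to verify that the two treatment groups are homogenous and in order to test for potential bias" arising from drop-outs or missing values. The test is given two jobs: to confirm that the arms are comparable, and to judge whether loss of participants has distorted the comparison.
- **Statistical analysis:** the design is a repeated-measures analysis of variance, with ANOVA and ANCOVA as the main tools. Treatment group is the main factor, and the baseline value is named, without condition, as the next in importance. For everything else, "Relevant characteristics will be added if applicable as covariates to the models".
- **Discussion:** "Due to the high expected attrition rate in this population at risk, drop-out is thoroughly documented and respective analyses are being planned".

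The Assessments and Outcome sections fix what can serve as a baseline. At t1, the start of the intervention, the families complete the BAMF sociodemographic questionnaire with the Hertie Belonging Scale. Hair cortisol is first taken a week before kindergarten entrance. LiSe-DaZ and SDQ are taken once, at t6.

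**The concern.** A significance test asks whether the data contradict equality. Failing to contradict it is not evidence of equality unless the test had a good chance of finding a difference large enough to matter. In a trial sized for an effect of 0.5 SD, it does not have that chance for imbalances of 0.2 to 0.3 SD, which can shift an unadjusted estimate appreciably.

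The natural safeguard is adjustment for prognostic baseline variables, whatever the balance looks like. The plan has this for the mothers' integration, where BAMF and Hertie items exist at t1. It cannot have it through the baseline value for the three child primary outcomes, which have no t1 measurement. At stake are an unnoticed shift in the estimate, precision given up on those three outcomes, and attrition bias passed over because a weak test did not flag it.

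**Working it through.** **Inputs (Sample size calculation section).** Alpha and power: "0.05 at a power of 0.80". Effect: "we expect effect sizes of at least *d* = 0.5". Cluster sizes: "the estimated coefficient of variation is *CV* = 0.4", ICC 0.1, mean cluster size 2, drop-out 20%. Sidedness is not stated; two-sided is assumed because it reproduces the plan's 63 (one-sided gives 50).

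**The plan's own figure.** Design effect = 1 + [(1 + 0.4²) × 2 − 1] × 0.1 = 1.132. Then 63 × 1.132 = 71.32, so 72, and 72 × 1.25 = 90 per arm. This reproduces exactly and is not affected by the point.

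**Power of a baseline homogeneity test.** SE = √(1.132 × 2/90) = 0.159 SD. Power = Φ(d/SE − 1.96), the opposite tail being negligible except at small d.

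- d = 0.2: 24%
- d = 0.3: 0.3/0.159 = 1.89, and Φ(1.89 − 1.96) = 47%
- d = 0.5: 88%

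Any observed imbalance up to 1.96 × 0.159 = 0.31 SD is non-significant. Using 1.132 assumes that the baseline variable clusters like the outcome. With no clustering the power at 0.3 SD is 52%, so the conclusion does not depend on this.

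**Power of a leaver-versus-completer test.** 20% of 180 is 36 leavers, which leaves 144. SE = √(1.132 × (1/36 + 1/144)) = 0.198.

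- d = 0.2: 17%
- d = 0.3: Φ(1.51 − 1.96) = 33% (36% without the design effect)
- d = 0.3 within one arm, 18 against 72: 19%

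For loss of 15% against 25% between arms (illustrative, averaging the planned 20%), the effective size is 90/1.132 = 79.5 per arm. The null SE is 0.0634 and the alternative SE 0.0630. Power = Φ((0.10 − 1.96 × 0.0634)/0.0630) = 35%.

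**What an unflagged imbalance can do.** If a covariate correlates ρ with the outcome (an assumption; the article gives no value), an imbalance of x SD shifts the unadjusted estimate by ρx. At the 0.31 SD limit:

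| ρ (assumed) | Shift (SD) | Share of d = 0.5 |
|---|---|---|
| 0.3 | 0.09 | 19% |
| 0.5 | 0.16 | 31% |
| 0.7 | 0.22 | 44% |

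**The opposite error.** Ten independent tests under correct randomisation give 1 − 0.95¹⁰ = 40% chance of at least one false signal of imbalance.

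**Gain from fixed adjustment.** With 72 analysed per arm, effective n = 72/1.132 = 63.6, and power = Φ(0.5 × √(63.6/2)/√(1 − R²) − 1.96). R² is assumed, with the design effect unchanged.

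- R² = 0: 0.805
- R² = 0.10: 0.84
- R² = 0.25: 0.90

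**The case against.** The strongest reply is that only one verb is too strong and the rest belongs in an analysis plan not shown here. Much of this is fair. A published protocol need not list covariates or missing-data methods, and their absence is not the point. The point is that the article does state a method for judging comparability and attrition bias, and that method cannot do the job.

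The size can also be disputed. Under correct randomisation an imbalance of 0.3 SD or more on a given covariate arises only about 6% of the time, and the nominal type I error already allows for chance imbalance. The table above is therefore what could pass unnoticed, not an expected bias. The correlations are assumed. Length of stay and knowledge of German are narrowed by eligibility, which may hold R² down. LiSe-DaZ norms already allow for age and length of exposure to German.

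A reader might also infer more than the text supports:

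- **That drop-out is taken to be harmless.** The article tests for bias and plans further analyses.
- **That the homogeneity tests select the covariates.** Nothing links the two sections; the conditional wording only leaves the choice open.
- **That all covariate adjustment is conditional.** The baseline value is named outright.
- **That every child with a missed visit is lost.** LiSe-DaZ and SDQ are measured once, so this cannot apply to them. For repeated measures it is a property of the classical method, not a stated rule.
- **That randomisation was unstratified, or that intervention B has no home visits.** Both are silences in the text.

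**Conclusion.** The concern holds in a limited form. As stated, the homogeneity tests can neither establish that the arms are alike nor exclude attrition bias: power is 47% for a 0.3 SD imbalance and about 33% for a 0.3 SD leaver-completer difference. These two figures rest on the plan's own inputs, two-sided testing, and the outcome's design effect applied to the tested variables.

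For hair cortisol, LiSe-DaZ and SDQ the named baseline factor is unavailable, so baseline adjustment depends on characteristics that the article neither names nor commits to. The gain from fixing them, from about 0.80 to between 0.84 and 0.90, is conditional on an assumed R² of 0.10 to 0.25.

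Differential loss between the arms is a possibility that the analysis should be ready for, not a documented fact. Neither the sample size nor the validity of the randomised comparison is called into question.

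**What to change.** 1. Replace the homogeneity tests between arms with a table of standardised differences, and drop the claim that comparability is verified.
2. Adjust each primary model for a short list of t1 characteristics fixed before outcome data are seen, and keep it whatever the observed balance. Candidates are centre and maternal sociodemographic items from the BAMF questionnaire. Keep the baseline value for the mothers' outcomes.
3. For hair cortisol, and for EAS among the secondary outcomes, use a mixed model that keeps children with some occasions missing, in place of classical repeated-measures ANOVA.
4. State the missing-data assumption for each primary outcome and add a sensitivity analysis for loss that depends on arm. Report leavers and completers descriptively.

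The cost is a change of analysis wording and slightly more analysis work. Centre is known from recruitment and the BAMF questionnaire is already given at t1. The article does not list the questionnaire's items, so the chosen ones should be checked against it.

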### Randomization

As Fig. 2 shows, randomization was performed at cluster level (integration course). A cluster-randomization was applied instead of a single randomization, because women from the same integration course should be assigned to the same intervention and not to different interventions. The statisticians, uninformed about the identity of the integration courses, used a table of random numbers for randomizing the 90 integration courses included in the study. Individual participants (children and their parents) were not aware of their group assignment, that is, if they were participating in the psychoanalytical intervention or the intervention provided by paraprofessionals.

### Statistical analysis

The design is an analysis of variance design with repeated measures. The main instruments for analysis applied are Analysis of variance (ANOVA) as well as Analysis of covariance (ANCOVA) models. The main factor is the intervention group (A or B) and the most relevant secondary factor is the initial value (baseline value). All baseline characteristics will be described at the individual level. Relevant characteristics will be added if applicable as covariates to the models. Six main assessments encompass the treatment phase and follow-up.

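### For hair cortisol, the named repeated-measures ANOVA in its classical form keeps only children with all three samples; a mixed model would use every measured value

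*Protocol article*

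**What the plan says.** Protocol article, Statistical analysis: "The design is an analysis of variance design with repeated measures". ANOVA and ANCOVA are named as the main instruments, with intervention group as the main factor, the initial value as the next most relevant factor, and further characteristics as covariates where applicable. The section gives no rule for incomplete data.

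Hypotheses on primary outcome and Primary outcome: Hypothesis 1 expects lower hair cortisol in arm A at t5 and at t6, from samples a week before kindergarten entrance, 6 weeks after it and 1 year after it. LiSe-DaZ and SDQ (Hypotheses 2 and 3) are measured once, at t6. The mothers' outcomes (Hypotheses 7 and 8) are assessed at t5.

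Sample size calculation: "Thus the minimum sample size would be 72 pregnant women per treatment"; with a 20% "drop-out rate the corrected minimum sample size is" 90 women per treatment.

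Discussion: "Due to the high expected attrition rate in this population at risk, drop-out is thoroughly documented", and related analyses are said to be in planning. The section on representativeness of the sample plans homogeneity tests, partly to look for bias from drop-outs or missing values.

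**The concern.** The objective is to compare A with B in the families that were randomised. In its classical form, repeated-measures ANOVA works on complete sets of values. For hair cortisol, a child with the first sample but without the last contributes nothing, not even to the t5 comparison that Hypothesis 1 names.

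Two things are at stake. Measured t5 and 6-week values are discarded. The remaining comparison is also exposed to any difference between arms in who leaves. Such a difference is conceivable, because intervention A adds telephone contacts and home visits to its weekly groups while intervention B consists of self-organised open groups. The article does not say that retention will differ. Homogeneity tests can reveal an imbalance, but they do not alter the estimate.

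**Working it through.** **1. The plan's own figures.** Inputs from the sample size section: alpha 0.05 (two-sided assumed, since it reproduces the result), power 0.80, d = 0.5, m = 2, CV = 0.4, ICC = 0.1.

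- Unadjusted n per arm: 2 × (1.960 + 0.842)² / 0.5² = 62.8, so 63 as stated.
- Design effect: 1 + [(1 + 0.4²) × 2 − 1] × 0.1 = 1 + 1.32 × 0.1 = 1.132.
- 1.132 × 63 = 71.32, so 72; 72 / 0.8 = 90. All steps reproduce.

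**2. Power with complete cases.** Power = Φ(0.5 × √(n_eff / 2) − 1.960), where n_eff = n / 1.132.

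| Complete per arm (of 90) | Loss | n_eff | Power |
|---|---|---|---|
| 81 | 10% | 71.6 | 0.849 |
| 72 | 20% (plan) | 63.6 | 0.805 |
| 63 | 30% | 55.7 | 0.751 |
| 54 | 40% | 47.7 | 0.685 |

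The t distribution gives 0.80 at 72 and 0.84 at 81. At the planned loss there is no shortfall. If half of the 20% loss falls after the t5 sample (an assumption), 90 × 0.9 = 81 children per arm have a t5 value, against 72 with all three. Using all t5 values then raises power for that comparison from about 0.80 to about 0.84.

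**3. Bias of the complete-case difference.** Let a share p of an arm leave, and let leavers be Δ worse than stayers. The stayers' mean is then better than the whole arm's mean by p × Δ. With the same Δ in both arms, the error in the A-B difference is (p_A − p_B) × Δ.

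- Assumed 15% versus 25%, Δ = 0.5 SD: 0.10 × 0.5 = 0.05 SD, or 10% of d = 0.5.
- Same split, Δ = 1.0 SD: 0.10 × 1.0 = 0.10 SD, or 20% of d = 0.5.
- Equal drop-out and equal Δ: 0.

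The direction depends on which arm loses more.

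**4. Drop-out that depends on the first sample (simulation).** Assumptions: three samples with pairwise correlation 0.3 to 0.7; true difference −0.50 SD throughout; 20% of each arm lost after the first sample; where drop-out depends on the first value, its log-odds rise by 1 per SD.

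| Dependence on the first value | Complete-case difference, mean of 3 samples | Missing-at-random estimate, last sample |
|---|---|---|
| Neither arm, or both arms alike | about −0.50 | about −0.50 |
| Arm B only | −0.36 to −0.41 | about −0.50 |
| Arm A only | −0.60 to −0.64 | about −0.50 |

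Equal drop-out rates therefore do not protect the complete-case result if the reasons for leaving differ by arm. An estimate that uses the first sample of the leavers recovers the true difference under these assumptions.

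**The case against.** The strongest objection is that the article never says an incomplete family is dropped. Deletion is inferred from the classical form of the method, and missing-data rules are commonly left to a full protocol or SAP, neither of which is shown. That stands as a limit: silence on imputation is no finding. The article does name the model, however, and that choice largely decides whether partial data are used. ANCOVA is named too, so separate analyses at t5 and t6 are not excluded; if those are meant, the text should say so.

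A reader might infer several stronger points that the document does not support:

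- **That the whole primary analysis rests on families who stayed to the end.** LiSe-DaZ and SDQ are single t6 measurements, so a missed earlier visit does not remove a child, and the mothers' outcomes are measured at t5. Deletion across visits concerns hair cortisol only.
- **That the trial itself expects attrition related to risk or outcome.** The Discussion speaks of high attrition in a population at risk, not of leaving because of stress or outcome.
- **That the step from 72 to 90 shows complete-case analysis.** It is a routine allowance under any method.
- **That the contrast is unbiased only if data are missing completely at random.** Steps 3 and 4 show about no bias when the pattern is the same in both arms.

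The planned homogeneity tests and drop-out analyses count in the plan's favour. The latter are not described, so one can say only that they are not shown to correct the estimate. Covariate adjustment helps where missingness depends on the covariates used, but no cortisol value exists from before the intervention.

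**Conclusion.** The point holds for hair cortisol. The named method, read in its classical form, discards measured t5 and 6-week values and leaves the A-B difference open to bias from drop-out that differs between arms in its rate or in its relation to outcome. The document neither states nor excludes such a difference.

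The size is moderate and rests on assumptions: 0.05 to 0.10 SD under the 15% versus 25% split, and 0.09 to 0.14 SD (0.50 − 0.41 to 0.50 − 0.36, similarly 0.60 − 0.50 to 0.64 − 0.50) when drop-out depends on the first value in one arm only. Planned power is not in question at 20% loss. The change is worth making because it is a better method at little cost, not because the stated one is shown to fail.

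**What to change.** For hair cortisol, replace the repeated-measures ANOVA with a linear mixed model on all randomised children with at least one sample. Include arm, time and arm by time, an unstructured within-child covariance, and integration course as a random effect. Report the A-B difference at t5 and at t6 from this model, and keep the complete-case ANOVA as a sensitivity analysis.

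For the outcomes measured at one time (LiSe-DaZ and SDQ at t6, mothers' outcomes at t5), multiple imputation by arm is an optional sensitivity analysis. It can draw on the t1 BAMF items and the HBS-L, EAS and Bayley values already collected.

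The cost is a change of wording and some programming, with no new data. The mixed model relies on data missing at random given the recorded values, a weaker assumption than missing completely at random. It does not recover children lost before their first hair sample.

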### Design

Figure 2 summarizes the study design. The individual participants (children and their parents) were not aware of their group assignment, that is, if they were participating in intervention A (FIRST STEPS) or in intervention B. The integration courses which the women are attending are randomly assigned to the two different interventions A and B, because women from the same integration course cannot be referred to different interventions (cluster-randomization).

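### Courses are randomised and the sample is sized for clustering, but the stated ANOVA/ANCOVA makes no allowance for course; at the plan's own ICC a 5% test runs at about 6.5%

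*Protocol article*

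**What the plan says.** Three parts of the protocol article bear on this.

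- **Design and Randomization.** The unit of allocation is the course: "The integration courses which the women are attending are randomly assigned to the two different interventions A and B". The statisticians "used a table of random numbers for randomizing the 90 integration courses included in the study".
- **Sample size calculation - power analysis.** The calculation "is based on *α* = 0.05 at a power of 0.80", with an expected effect of d = 0.5, which gives 63 per arm before clustering. It then applies a correction for unequal clusters (ICC 0.1, CV 0.4, mean of 2 women per course), using a formula described as "providing a conservative estimate of sample size requirements for trials using cluster-level analyses weighted by cluster size". The result is 72 per arm, or 90 after 20% dropout.
- **Statistical analysis.** The design is described as analysis of variance with repeated measures, and "The main instruments for analysis applied are Analysis of variance (ANOVA) as well as Analysis of covariance (ANCOVA) models". On the terms of the model: "The main factor is the intervention group (A or B) and the most relevant secondary factor is the initial value (baseline value"). Further characteristics may enter as covariates. The section names no course factor, random effect, cluster summary or cluster-robust variance, and no other section supplies one for the outcome analysis.

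**The concern.** The sample was enlarged because women from the same course are expected to resemble each other. The stated model has no means of recognising that resemblance. An ANOVA or ANCOVA on arm, baseline and covariates, run on women or children as the units, treats course-mates as independent. The model standard error is then smaller than the true one whenever the course ICC is positive, intervals are too narrow, and the test rejects a true null more often than 5% of the time. This affects the main comparisons between arms. In a superiority trial whose result is meant to inform a wider rollout, the excess false positives include findings in favour of intervention A.

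**Working it through.** **Inputs, all from the sample size section:** α = 0.05, power 0.80, d = 0.5, CV = 0.4, ICC = 0.1, m = 2, dropout 20%. Sidedness is not stated. Two-sided is taken because it reproduces the plan's 63, whereas one-sided gives 50.

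**Step 1: reproduce the plan's figure.**
- Unadjusted: n = 2 × (1.960 + 0.842)² / 0.5² = 62.8, so 63 per arm.
- Design effect: DE = 1 + [(1 + 0.4²) × 2 − 1] × 0.1 = 1 + 1.32 × 0.1 = 1.132.
- Corrected: 1.132 × 63 = 71.32, so 72 per arm. With dropout: 72 × 1.25 = 90.

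The plan's arithmetic is right.

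**Step 2: error rate if course is ignored.** The true standard error is √DE = √1.132 = 1.064 times the model's. The model's is therefore 1/1.064 = 0.940 of the true one, about 6% too small. The actual two-sided error is

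2 × [1 − Φ(1.960 / 1.064)] = 2 × [1 − Φ(1.842)] = 0.0655.

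**Step 3: dependence on the ICC.** Only 0.1 is the plan's value; the others are assumptions. A range is worth showing because the plan bases its 0.1 on pre-post differences, while hair cortisol, LiSe-DaZ and SDQ are first measured at t5 or t6.

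| Course ICC (m = 2, CV = 0.4) | DE | True/model SE | Actual error |
|---|---|---|---|
| 0.01 (assumed) | 1.013 | 1.007 | 5.15% |
| 0.05 (assumed) | 1.066 | 1.032 | 5.8% |
| 0.1 (plan) | 1.132 | 1.064 | 6.5% |
| 0.2 (assumed) | 1.264 | 1.124 | 8.1% |

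If dropout thinned courses to a mean of 2 × 0.8 = 1.6 women (assumed), DE at ICC 0.1 would be 1.086 and the error 6.0%.

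**Step 4: simulation.** 40,000 trials per setting, with no true effect and course sizes of 1 to 3 (mean 2, CV 0.4). At ICC 0.1 the test that ignores course rejected in 6.5% of trials with 36 courses per arm and 6.3% with 45. A course-level analysis weighted by course size rejected in 5.3% and 5.1%.

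**Step 5: power once course is accounted for.** The effective size is 72 / 1.132 = 63.6 per arm. Power = Φ(0.5 × √(63.6 / 2) − 1.960) = Φ(0.860) = 80.5%. The planned sample already pays for the adjustment.

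**The case against.** The strongest reply is that the analysis section is a short summary in a journal article, and that a fuller plan may exist. ANOVA and ANCOVA can be run on weighted course means, or with course as a nested random factor, so naming them does not exclude an adjustment. Variance estimators and degrees of freedom are commonly left to an analysis plan. Part of this stands: the article does not say that clustering will be ignored. But the section is not silent on the model. It names the model family and ranks the factors, and the randomised unit is absent from that ranking although the sample size section is built around it. That is a mismatch between two stated parts of the plan, not just a missing detail.

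Four stronger readings are tempting, and the document does not support them.

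- A reader might infer that the outcome analysis is declared to be at the level of the individual. The phrase appears only in "All baseline characteristics will be described at the individual level", which concerns descriptive tables.
- A reader might say that arm and baseline are the only terms. Optional covariates are also allowed.
- A reader might conclude that every p-value is too small. The bias depends on each outcome's course ICC and vanishes as that approaches zero.
- A reader might add correlation from the weekly intervention groups and arrive at a much larger inflation. The document gives neither the number of women per group nor a group-level ICC, so no figure for this can be drawn from it. It is also a different question from the randomised course.

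**Conclusion.** The point holds in limited form. The plan randomises courses and sizes the trial for a cluster-level analysis, then names an outcome model with no allowance for course. Followed as written, the nominal 5% two-sided test runs at about 6.5% at the plan's own ICC, mean cluster size and CV, with a standard error about 6% too small. This rests on three assumptions: a two-sided test, analysis of individual outcomes without course adjustment (the natural reading of the named terms, though not stated in words), and a positive course ICC for the outcome concerned. The excess is modest because courses contribute only about two women each. It should still be corrected, since the plan itself expects the correlation and the correction is cheap.

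**What to change.** Bring the Statistical analysis section into line with the sample size section. State that each primary outcome is analysed in one of two ways:

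- the course-level analysis weighted by course size, which the sample size formula assumes; or
- a linear mixed model with a random intercept for integration course and small-sample degrees of freedom.

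For binary outcomes, such as the mothers' completion of the integration course, use GEE or a mixed logistic model with course as the cluster.

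The cost is a change of wording and intervals about 6% wider at the planned ICC. No extra participants are needed, since power at 72 analysed per arm stays at about 80%. Courses were the units randomised, so each family's course should be known. Fixed effects for recruiting centre and a random effect for intervention group are not needed to correct this mismatch: the Randomization section describes no stratification by centre, and the intervention groups are a separate matter.
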